# Electroacupuncture versus sham for insomnia in patients undergoing maintenance hemodialysis: study protocol for a pilot randomized controlled trial

**DOI:** 10.1080/07853890.2025.2496410

**Published:** 2025-04-29

**Keywords:** Insomnia, end-stage renal disease, maintenance hemodialysis, electroacupuncture, sham electroacupuncture

## Abstract

**Background:**

Insomnia causes severe health problems and poor quality of life in patients with end-stage renal disease (ESRD) undergoing maintenance hemodialysis (MHD). Conventional therapies are limited due to the poor availability and opaque evidence, and electroacupuncture (EA) is considered an alternative for improving insomnia in patients with ESRD undergoing MHD.

**Methods:**

This is a study protocol for a pilot randomized, sham-controlled, single-center, clinical trial. A total of 60 patients with insomnia in ESRD undergoing MHD will be randomly assigned to treatment group (EA, 3 sessions per week for 4 weeks), or sham group (sham EA, 3 sessions per week for 4 weeks) in a 1:1 ratio. Participants will complete the trial by visiting the research center at Week 8 for a follow-up assessment. The primary outcome is the response rate: the proportion of patients achieving a minimal clinically important difference, which is defined as ≥7 points on insomnia severity index (ISI) at Week 4 compared with baseline. Secondary outcomes include sleep diary, ISI, pittsburgh sleep quality index (PSQI), short form health survey-12 (SF-12), fatigue severity scale (FSS), 24-Hour ambulatory blood pressure, and plasma levels of C-reactive protein (CRP) and D-Dimer.

**Discussion:**

This is the first standardized protocol investigating the efficacy and safety of EA for patients with ESRD undergoing MHD. This trial may provide evidence for clinical application of EA for patients with ESRD undergoing MHD.

**Trial Registration:**

Chinese Clinical Trial Registry (registered number: ChiCTR2300071814).

## Introduction

1.

Insomnia is defined as persistent difficulty in falling or maintaining sleep or waking up too early despite adequate sleeping opportunities and circumstances for sleep, which produces impairment of daytime function. Chronic insomnia is characterized by sleeping disturbances occurring at least three times per week for at least 3 months [1].

Insomnia is one of the most common problems in patients with all stages of kidney dysfunction, and worsening chronic kidney disease (CKD) or end-stage renal disease (ESRD) is directly associated with worsening insomnia [2], which results in fatigue, impaired circadian rhythm, poor overall quality of life [3], and increased complications such as depression, impaired immune response [4]. Insomnia occurs in more than half of patients with predialysis CKD, with a prevalence of up to 69% in patients with ESKD [5]. Insomnia in ESRD patients is affected by a variety of factors, including elderly age, dialysis vintage and a higher parathyroid hormone level [6], in which, patients treated with maintenance hemodialysis (MHD) have ranked insomnia as one of the major issues that reduce their quality of life [5]. Studies have suggested that 40% to 85% of patients undergoing dialysis have sleep disturbances [7], and a study conducted in the US demonstrated that among 1,643 patients from 335 US dialysis centers, 50% had difficulty falling asleep, 59% woke during the night, and 49% woke up too early; 53% had one or more of these symptoms all or most of the time [8]. Insomnia in ESRD patients increases nocturnal systolic blood pressure variability (BPV) [9] and inflammatory factors such as high-sensitivity C-reactive protein (hsCRP), interleukin 1β (IL-1β) [10], which might contribute to disease progression and worsen prognosis. A study has demonstrated that poor sleep quality reduced patient’s quality of life and triggered higher mortality [11].

Currently, there is no specific nonpharmacologic or pharmacologic recommendation for insomnia management in MHD patients, the American College of Physicians recommends cognitive behavioral therapy for insomnia (CBT-I) as the first-line treatment for insomnia, including stimulus control, sleep restriction and consolidation, cognitive restructuring, and sleep hygiene [12,13]. However, there are few physicians trained in CBT-I and CBT-I will be an extra treatment burden for patients with MHD who already have extremely hectic treatment schedule. Therefore, CBT-I should be adjusted particularly for these patients, and physicians need to be further trained based on the unique circumstances of these individuals. Except for CBT-I, pharmacotherapy is commonly used in treating insomnia, whereas there is no consensus about which sleep medication should be recommended to MHD patients due to the limited evidence about efficacy and safety [3,7]. Although benzodiazepines and nonbenzodiazepine receptor agonists are often prescribed for MHD patients, attention should also be paid to the risk of side effects and death in MHD patients [14], for example, benzodiazepines may cause Alzheimer’s disease or stroke [15,16]. Besides, many physicians are reluctant to prescribe sleep medications for MHD patients because of the limited efficacy and safety data. Therefore, most patients with ESKD undergoing MHD who have insomnia do not receive any treatment, which causes a vicious cycle for them.

Alternative treatment such as acupuncture has been recognized with the efficacy and safety in treating insomnia [17]. A clinical trial has suggested electroacupuncture (EA) significantly improves the quality of sleep in patients with depression [18]. Moreover, acupuncture promotes renal function, reduces proteinuria, controls hypertension, corrects anemia, relieves pain, and controls many hemodialysis-related complications including insomnia in patients with CKD [19,20]. However, there is no clinical trial demonstrating the efficacy and safety of EA in treating insomnia in ESRD undergoing MHD, and a sham-controlled trial is considered by the systematic review to have a low risk of bias in all areas, including selection, conduct, detection, attrition and reporting [21]. Therefore, our study aims to investigate the efficacy and safety of EA in relieving insomnia in ESRD undergoing MHD using a randomized, sham-controlled clinical trial. We present this article in accordance with the SPIRIT reporting checklist.

## Methods/design

2.

### Study design and setting

2.1.

This study proposes a single-center, sham-controlled, randomized controlled trial (RCT) at Beijing Dongcheng First People’s Hospital. The study was approved by the research ethic committee. The study will undergo quarterly audits by the Ethics Committee to determine if early termination is necessary. This study will be conducted following the Declaration of Helsinki (as revised in 2013). Written informed consent will be obtained from all participants. Recruitment strategies include posting online advertisement *via* the hospital website and Chinese social media (WeChat), as well as flyers at outpatient unit [22,23]. The intervention includes 4 weeks of EA or sham EA and 4 weeks of follow-up (Figures 1 and 2).

**Figure 1. F0001:**
[figure not shown]
Flow diagram. BP: blood pressure, CRP: C-reactive protein, FSS: fatigue severity scale ISI: insomnia severity index, PSQI: Pittsburgh sleep quality index, SF-12: short form health survey-12.

**Figure 2. F0002:**
[figure not shown]
Schedule for data collection of this trial. X: the moment of enrolment, intervention or assessments. Double-headed arrows: the whole phase of intervention or adverse events assessment. BP: blood pressure, CRP: C-reactive protein, FSS: fatigue severity scale ISI: insomnia severity index, PSQI: Pittsburgh sleep quality index, SF-12: short form health survey-12.

### Participants

2.2.

Participants will be recruited from the hemodialysis department of Beijing Dongcheng First People’s Hospital. The enrolment began in June 2023 and is anticipated to be completed by June 2024. Each eligible and consented patient will be randomly assigned in a 1:1 ratio to receive 4-week EA or sham EA.

#### Diagnosis criteria

2.2.1.

End-stage renal disease will be diagnosed based on ‘Practice Guideline for the Evaluation and Management of Chronic Kidney Disease (2012 Edition)’ [24]. Stage 5 chronic kidney disease or requirement of maintenance hemodialysis will be diagnosed based on ‘Guidelines for early screening, diagnosis, prevention and treatment of chronic kidney disease (2022 Edition)’ [25]. Insomnia will be diagnosed based on ‘Guidelines for diagnosis, treatment of insomnia in Chinese adults (2017 Edition)’ [26].

#### Inclusion criteria

2.2.2.

Aged between 18 and 75 years, male or femaleDiagnosed with end-stage renal disease and chronic insomnia based on the abovementioned diagnosis criteriaInsomnia Severity Index (ISI) ≥15Maintenance hemodialysis treatment ≥3 months with stable conditionAgreement of using zopiclone as rescue medicationProvision of written informed consent

#### Exclusion criteria

2.2.3.

Renal transplant patientsHaving hemorrhagic disease, neurological disease, metabolic disease, hematopoietic system disease, infectious disease or other severe acute or chronic organic diseasesHistory of long-term use of sleeping pills before hemodialysis treatmentHaving taken sleeping pills within 2 weeks before the first hemodialysis treatmentHaving unstable uremia complications such as water-electrolyte and acid-base disturbances, calcium and phosphorus metabolism disorders, cardiac insufficiencyHaving acupuncture therapy in the last 3 monthsHaving mental disorders or severe cognitive disordersPregnant or breastfeeding womenHaving taken part in other clinical trials within the past 3 monthsUnable to cooperate or unwilling to comply with all study requirementsWith cardiac pacemaker, metal allergy, or needle phobia

### Randomization and allocation concealment

2.3.

Participants will be randomly allocated in a 1:1 ratio to either the treatment group (EA) or control group (sham EA). An independent statistician, who will not be involved in the later implementation or statistical analysis, will generate the randomization sequence using block randomization with a block size of 6 or 4 *via* R software (4.2.1). The enrollment number will be written on the cover of an opaque envelope where the randomization sequence will be placed. The Research Center of Clinical Epidemiology (Beijing Institute of Traditional Chinese Medicine) will provide a randomization sequence and opaque envelopes. Researchers will be required to open the envelope according to the enrollment order of participants and apply the treatment instructions specified for their respective groups [22].

### Blinding

2.4.

Throughout the trial, participants will be blinded, however, acupuncturists will not be blinded due to the nature of the intervention. Blinding of group assignments will also be enforced for data analysts and outcome assessors. The concealment of the allocation for all participants will be maintained until the statistical analysis has been completed.

### Interventions

2.5.

The style of acupuncture is based on traditional Chinese medicine principle, and acupuncture prescription has been developed from literature review [27] as well as the clinical practice. Each participant will be ushered by a research assistant to hospital bed, which will be screened off separately one-by-one by opaque curtains. No companion will be allowed to stay with the participants during the treatment period. Acupuncturists should have a Chinese medicine practitioner license with at least 2 years of experience, and two acupuncturists will be given trial-specific training, such as the selection of acupuncture points and the usage of EA apparatus in different groups at the program launching session to realize their role and job in this study. Each participant will be performed EA or sham EA by the same acupuncturist throughout the trial. Also, two acupuncturists will not tell anyone else about the treatment allocation, and they will be asked to communicate with participants as less as possible to avoid inadvertent unblinding.

Sterile disposable acupuncture needles (length, 25–40 mm; diameter, 0.25–0.30 mm; Hwato Brand, Suzhou Medical Appliance Factory, Suzhou, China) and EA apparatus (HANS-200A acupoint nerve stimulator, Nanjing Jisheng Medical Co, Ltd) will be used in both groups. EA apparatus will be connected right after needles are inserted into all acupuncture points, and will be retained for 30 min. All participants will receive the same treatment according to their group. Both the treatment and sham groups will consist of 12-session intervention over 4 weeks (three sessions per week, ideally every other day). Intervention will be discontinued if the participants have any serious adverse events. All participants will be informed that the current of EA may not be perceived by human.

MHD treatment will be applied using sodium bicarbonate dialysate, dialyser (Braun Co, Ltd or Fresenius Co, Ltd, German), and disposable dialyzer membranes (diacetate membrane or polysulfone membrane) in both groups. The dialysate flow rate will be 500 ml/min and blood flow rate will be 200–250ml/min. The frequency will be 3 times per week with 3.5 to 4-h duration each time. The vascular access includes arteriovenous fistula (AVF), arteriovenous graft (AVG), long-term central vein catheter (CVC), and temporary CVC. Unfractionated heparin (UFH) or low-molecular-weight heparin (LMWH) will be applied as an anticoagulant to all participants. Other supportive interventions include treatments for underlying diseases and complications such as hypertension, diabetes, infections, renal anemia, and water and electrolyte metabolism disorders.

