#### Treatment group

2.5.1.

Acupoints of Baihui (GV20), Shenting (GV24), Sishencong (EX-HN1), bilateral Benshen (GB13), Shangwan (CV13), Zhongwan (CV12), Xiawan (CV10), Qihai (CV6), bilateral Tianshu (ST25), bilateral Neiguan (PC6), bilateral Shenmen (HT7), and bilateral Zusanli (ST36) will be used in EA group (locations are shown in Table 1 and Figure 3). With participants in a prone position, acupuncturists will use 75% alcohol pads to sterilize the skin around the acupoints and then insert disposable needles into the acupoints. For Baihui (GV20), Shenting (GV24), Sishencong (EX-HN1), bilateral Benshen (GB13), the needles will be inserted approximately 5–10 mm with a 30° angle between the needle tip and the scalp, for Shangwan (CV13), Zhongwan (CV12), Xiawan (CV10), Qihai (CV6), bilateral Tianshu (ST25), bilateral Neiguan (PC6), bilateral Shenmen (HT7), and bilateral Zusanli (ST36). Needles will be inserted at an angle of 90° and a depth of 20–30 mm. Lifting and thrusting combined with twirling and rotating will be performed for at least 10 s per acupoint to reach the De qi sensation (soreness, numbness, distention, and heaviness). Then a pair of electrodes from the EA apparatus will be connected to the needle handles at Baihui (GV20), Shenting (GV24). The EA waveform adopts 2/100 hz density alternating wave and the intensity of electric current will be regulated until the participants can perceive and tolerate it. Immediately after needle removal, acupuncturists will gently press acupoints with dry sterilized cotton balls to avoid bleeding.

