#### Sham group

2.5.2.

Twenty non-acupoints based on literature review [28,29] and the clinical practice will be used in sham group (locations are shown in Table 2 and Figure 4). Participants will use an opaque patch to cover their eyes and lie in a prone position, acupuncturists will use 75% alcohol pads to sterilize the skin around the acupoints and then insert disposable needles into the acupoints. Needles will be inserted at an angle of 90° and a depth of 2–3 mm (superficial penetration) in acupoints located in face and will be inserted at an angle of 90° and a depth of 2–3 mm in acupoints located in limbs and abdomen without any manipulation like lifting and thrusting or twirling and rotating to avoid De qi sensation. The sham electrodes from the EA apparatus will be connected to the needle handles at non-acupoint 1 (NA1) and NA2. The sham electrode lines will be identical to the real one, but the inner metal wires will be cut off. Therefore, no current will be outputted with the EA apparatus in a power-on state with a lighted power indicator and voice of clatter. The parameters of sham EA apparatus and treatment will be the same as in the EA group. Participants will be treated individually to avoid communication.

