**Figure 4. F0004:**
[figure not shown]
Locations of acupuncture points used in sham electroacupuncture group. Yellow dots: acupoints used for locating non-acupoints; blue dots: non-acupoints. NA: Non-acupoint, GB14: Yangbai, SJ6: Waiguan, CV15: Jiuwei, CV12: Zhongwan, CV9: Shuifen, CV5: Shimen, LU6: Kongzui, GB34: Yanglingquan, SP6: Sanyinjiao.

**Table 2. t0002:** Locations of non-acupuncture points used in sham electroacupuncture group.

Non-acupoints	Location
NA1-2	3 cun lateral to the GB14 (On the forehead, 1 cun directly above the midpoint of the eyebrow) horizontally.
NA3-4	1 cun lateral to the CV15 (Below the xiphoid process, 7 cun above the umbilicus, locate the point in supine position with the arms uplifted) horizontally.
NA5-6	1 cun lateral to the CV12 (On the midline of the abdomen, 4 cun above the umbilicus) horizontally.
NA7-8	1 cun lateral to the CV9 (On the midline of the abdomen, 1 cun above the umbilicus) horizontally.
NA9-10	1 cun lateral to the CV5 (On the midline of the abdomen, 2 cun below the umbilicus) horizontally.
NA11-12	On the side of the abdomen, 2 cun above the anterior superior iliac spine.
NA13-14	1 cun lateral to the SJ6 (3 cun above SJ 4, between the radius and the ulna, on the radial side of muscle extensor digitorum) horizontally.
NA15-16	3 cun lateral to the LU6 (The point is on the palm aspect of the forearm, on the line joining Lu 9 and Lu 5, 7 cun above the transverse crease of the wrist) horizontally.
NA17-18	3 cun inferior to the GB34 (In the depression anterior and inferior to the head of the fibula) vertically.
NA19-20	1 cun inferior to the SP6 (3 cun directly above the tip of the medial malleolus, on the posterior border of the medial aspect of the tibia) vertically.

NA: Non-acupoint, GB14: Yangbai, CV15: Jiuwei, CV12: Zhongwan, CV9: Shuifen, CV5: Shimen, SJ6: Waiguan, LU6: Kongzui, GB34: Yanglingquan, SP6: Sanyinjiao.

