There are several limitations in our study. First, the acupuncturists are not blinded. Therefore, acupuncturists may pay more attention to the participants in the treatment group, which may lead to the observed effects. Also, we use sham EA with false apparatus and superficial penetration on non-acupoints to isolate the specific effect of EA. Compared with placebo control, there is a possibility of having a therapeutic effect. However, we hypothesize that EA will have a better effect, so there is no need to set a placebo control group, and the sham control procedure has been successfully applied in previous study [29]. Moreover, our study is single-center, participants are from one hospital, which will cause limited representativeness of patients and poor extrapolation of our findings. However, single-center study has better internal authenticity compared with multi-center trials. Besides, the relatively small sample size may reduce the probability of rejecting a false null hypothesis, whereas, our study is a pilot study, a sample size of 30 for each group is recommended in previous studies. Finally, due to the treatment burden of patients with ESRD undergoing MHD, a fixed treatment schedule will not be set for everyone, we will suggest participants receiving treatment every other day, however, treatment schedule will be adjusted when overlapping MHD treatment.

In conclusion, we will conduct a single-center and two-arm RCT to investigate the efficacy and safety of EA for insomnia in ESRD undergoing MHD. We employ a strict methodology to minimize bias and form monitoring committees to guarantee the quality of the clinical trial, which provides evidence for further understanding and generalizing the clinical application of EA for insomnia in ESRD undergoing MHD.

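### Participants with an arm fistula or graft are eligible, yet both groups' fixed point sets needle both forearms or wrists, with no rule sparing the access limb

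*Protocol article*

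**What the plan says.** **Population.** Section 2.5 (Interventions) states: "The vascular access includes arteriovenous fistula (AVF), arteriovenous graft (AVG), long-term central vein catheter (CVC), and temporary CVC". The inclusion and exclusion lists (2.2.2 and 2.2.3) contain no criterion on access type, limb or side.

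**Uniformity of treatment.** The same section says "EA apparatus will be connected right after needles are inserted into all acupuncture points" and "All participants will receive the same treatment according to their group".

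**EA points.** Section 2.5.1 prescribes "bilateral Neiguan (PC6), bilateral Shenmen (HT7), and bilateral Zusanli (ST36) will be used in EA group". Table 1 puts PC6 on the distal forearm, 2 cun above the wrist crease, and HT7 at the wrist crease. Both belong to the set needled at 90° to 20–30 mm, with at least 10 s of manipulation per point.

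**Sham points.** Section 2.5.2 prescribes twenty non-acupoints, with needles at "a depth of 2–3 mm in acupoints located in limbs and abdomen without any manipulation". In Table 2, points NA13-14 lie "1 cun lateral to the SJ6" and points NA15-16 lie "3 cun lateral to the LU6". Both reference points are on the forearm.

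**Adaptation to dialysis.** The only one stated concerns timing. The Discussion (section 3) says the "treatment schedule will be adjusted when overlapping MHD treatment".

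**The concern.** A fistula or graft is the participant's route for dialysis three times a week (section 2.5). The article admits patients with such an access, fixes needling in both upper limbs, and exempts no limb. Section 2.6.4 lists subcutaneous hematoma and infection among the common adverse events of acupuncture. It does not link them to the access, but nothing in the stated rule keeps needles out of the limb where such an event would matter most.

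There is also a smaller analytic issue. If the acupuncturists, who are not blinded, spare the access limb on their own judgement, no common rule governs what they do in the two groups. Section 2.6.3 scores compliance by sessions attended, so omitted needles would not show there. Section 2.8 restricts the per-protocol set to participants without major deviations and does not say whether leaving out points counts as one. This touches only a sensitivity analysis.

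**Working it through.** The plan gives no figure to reproduce on this point, so the check is a reading of the text and a count of needles.

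**1. Does the text, followed exactly, reach the access limb?**

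- Fistulas and grafts are named as accesses (2.5), and no criterion excludes them (2.2.2, 2.2.3).
- The EA points PC6 and HT7 are explicitly bilateral (2.5.1).
- The sham forearm points are numbered in pairs against a single location each (Table 2). One point per side is inferred from that numbering; Figure 4 is not available to confirm it.
- Section 2.5 calls for needles at every point and the same treatment within a group.
- No section omits, moves or makes unilateral any point.

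So a participant whose access is in an arm is needled in that arm, in either group.

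**2. Needles per session**

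| EA point | Needles |
|---|---|
| GV20 | 1 |
| GV24 | 1 |
| EX-HN1 | 4 |
| GB13, bilateral | 2 |
| CV13, CV12, CV10, CV6 | 4 |
| ST25, bilateral | 2 |
| PC6, bilateral | 2 |
| HT7, bilateral | 2 |
| ST36, bilateral | 2 |
| **Total** | **20** |

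Sham: NA1 to NA20 = 20 needles.

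**3. Needles in one arm**

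- EA: PC6 (1) + HT7 (1) = 2; 2/20 = 10%.
- Sham: one of NA13-14 + one of NA15-16 = 2; 2/20 = 10%.
- Over 12 sessions: 2 × 12 = 24 insertions in the access arm, in either group.

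**4. Effect of omitting the access-limb points**

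| | EA | Sham |
|---|---|---|
| Arm access, per session | 20 − 2 = 18 | 20 − 2 = 18 |
| Arm access, 12 sessions | 18 × 12 = 216 of 240 | 18 × 12 = 216 of 240 |
| Leg access, per session | 20 − 1 (ST36) = 19 | 20 − 2 (one of NA17-18, one of NA19-20) = 18 |

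The electrode pairs (GV20 and GV24 in EA, NA1 and NA2 in sham) are on the head and do not change.

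**The case against.** The strongest reply is that this is a condensed article. Point-by-point precautions may sit in the full protocol or in the training that section 2.5 mentions, which covers the selection of points. On this view the sentence about inserting needles merely orders the steps, and the one about uniform treatment merely announces a standardised prescription. It is a fair reading of those two sentences. It leaves untouched the explicit bilateral prescription in section 2.5.1, to which no section makes an exception. If the full protocol does exempt the access limb, the article misstates the plan and still needs correcting.

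Second, the article names no hazard specific to a fistula or graft, and the counts measure exposure, not harm. Both points are true. The concern rests on what the document itself gives: hematoma and infection as common acupuncture events, and a limb needed for dialysis three times a week. It does not rely on heparin still acting at the time of needling, which the article does not address.

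Third, the sham exposure is milder, at 2–3 mm without manipulation, and its laterality is inferred. Both limits stand. The EA side does not depend on that inference.

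Fourth, there are general safeguards: exclusion of hemorrhagic disease, pressure after needle removal in the EA group, adverse-event checks after each session, stopping for serious events, and quarterly ethics audits. None of them determines where needles go.

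Fifth, enrolment was expected to finish by June 2024 and the article appeared in April 2025, so a new needling rule may protect nobody in this trial. This stands, and it changes which remedy applies.

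**Conclusion.** The concern holds and should be fixed. As written, the needling rule places 2 of 20 needles per session, 24 insertions over 12 sessions, in the limb of any participant whose fistula or graft is in an arm. Depth is 20–30 mm with manipulation in the EA group and 2–3 mm without in the sham group.

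The conclusion is conditional on the access being in an arm. The article does not say which limb bears the access or how often it is an arm, so the number of participants affected is unknown. The sham count also assumes one point of each pair per side.

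This is a safety point. The primary intention-to-treat comparison is not affected, and the consequence for the per-protocol sensitivity analysis is small.

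**What to change.** Record access type, limb and side at baseline. Add a rule to sections 2.5, 2.5.1 and 2.5.2 along these lines:

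> In both groups, no needle is placed in a limb that bears an AVF or AVG. In the EA group this drops PC6 and HT7 on that side, or ST36 for a leg access. In the sham group it drops the NA13-14 and NA15-16 points on that side, or the NA17-18 and NA19-20 points for a leg access. Such an omission is not a protocol deviation.

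Qualify the two uniformity statements in section 2.5 to match. If the full protocol already contains such a rule, correct the article to say so.

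If enrolment has ended, report by group how access limbs were handled, and classify any omitted points as non-major before the per-protocol analysis is run.

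The cost is one baseline field and a few sentences, or one reporting table by group. No extra staff, procedures or patients are needed. The downside is that the point set is no longer identical for everyone: a participant with an arm access loses two needles on one side and keeps the corresponding points on the other. For a leg access the groups would differ by one needle per session (19 against 18).
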